#### Adverse effects

Potential adverse effects of tDCS will be assessed at the end of each session using a questionnaire administered to the child. The questionnaire will address the perception of symptoms that occurred during the session, such as tingling, itching, burning sensation, headache, pain at the electrode site, drowsiness, and altered mood. The participants will be instructed to respond using a three-point scale. Caregivers and children will also receive open-ended questions at the beginning of each session addressing the occurrence of headache, scalp pain, itching, burning sensation, redness of the skin, drowsiness, difficulty concentrating, and mood swings between sessions.

### Virtual reality

Training sessions combined with tDCS will be held three times a week on non-consecutive days. Each session will last 20 min. Two training sessions will be held before the start of the intervention protocol to familiarize the participants with the procedures. Records will be made of the number of sessions attended, the duration of each session and the final score of the game based on the number of correct and incorrect taps on the screen. The entire training protocol will be carried out by a project employee with interests independent of the objective of the study.

The game will consist of five balls displayed on a touch screen. When the game starts, one of the balls will change color. At that moment, the child must touch the respective ball. After the child touches the screen, the ball returns to its original color and another ball will change color after a three-second interval. The game will consist of seven blocks: R1, R2, S1, S2, S3, R3, and S4. R blocks are those with random sequences and S blocks are those with repetitive sequences, with each block consisting of 20 sequences. A sequence is the order in which the balls change color. The sequences are either random or repetitive, depending on the block. Each sequence will be composed of five touches, such that 100 touches are performed by the end of each block.

Among the parameters obtained from the game for the analysis of the learning process in children with DS, the error will be calculated. The error is obtained by calculating the distance between the center of the ball and the region touched as well as the time interval between the moment that the ball changes color and the child's touch. The total error is given by the sum of the time interval and the distance between points (touch and center of the ball) for each event.

To ensure the synchronization of the game, the acquisition of the EEG signals, the motion reconstruction and the EMG system, it will be necessary for a pulse to be sent with each child's touch. This pulse will be interpreted by an Arduino platform, which will subsequently send the information to both systems [49, 50].

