### Recruitment

Strategies will be employed to encourage participation in the study and reduce the dropout rate. The children with DS will be recruited from the outpatient clinic of the University Center of Anápolis and the Association of Parents and Friends of Exceptional Children of Anápolis. Parents/guardians will be contacted by telephone (or other means of communication). Pamphlets will be created with a brief description of the objectives, type of therapeutic intervention, expected results and eligible population. The researchers of the project will be responsible for this disclosure as well as leaving contact information for the parents of eligible children. The children selected for this study will be recruited according to the schedule registered with the ethics committee and REBEC in December 2020.

#### Study 1

A cross-sectional study will be conducted to determine the pattern of normality in children with typical development and compare the pattern to that found in children with DS. The sample selected for this study will be in accordance with the eligibility and quantity criteria for a convenience sample. The participants will be divided into two groups and each group will consist of 12 children.

#### Study 2

A pilot study will be conducted to determine the sample size for the randomized controlled clinical trial. For the proper sample size calculation, the pilot study will be carried out using the same methods as those to be employed in the main study and will involve ten children selected based on the eligibility criteria for the children with DS. The sample size for the clinical trial will be calculated based on the means obtained in the experimental and control groups of this pilot study, considering brain activity as the primary outcome, a unidirectional alpha of 0.05 and a power of 80%. The sample size will be then increased by 20% to compensate for possible dropouts.

#### Study 3

A randomized controlled trial will be conducted. The sample will be selected based on the results of the pilot study and the children will be randomly distributed into two groups using a randomization website (www.random.org).

The experimental group is as follows: anodal tDCS (anode placed over F3 of the International 10-20 Electroencephalogram System and cathode placed over right deltoid muscle) combined with VR training.

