## Statistical analysis of results

Statistical analysis will involve the calculation of mean, standard deviation, minimum and maximum values for the descriptive analysis of the effects of tDCS and VR on the quantitative variables. The Shapiro-Wilk normality test will be used to determine the distribution of the data in terms of adherence to the Gaussian curve. Parametric variables will be expressed as mean and standard deviation. Nonparametric variables will be expressed as median and interquartile range.

For phase 1, either Student’s *t*-test or Mann-Whitney test will be used to compare quantitative variables between the TD and DS groups. In phase 2, descriptive measures of mean and standard deviation will be used as initial values for the calculation of the sample size in phase 3. In phase 3, we will analyze quantitative variables with measures over time (pre-intervention, post-intervention and one-month follow-up) and comparisons of the EG and CG will be performed using repeated-measures ANOVA. The level of significance will be set at 5% for all statistical tests. The data will be organized, tabulated and analyzed with the aid of the Statistical Package for the Social Sciences (v.25.0).

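### The game parameter total error adds a response time to a touch distance with no scaling, so the units chosen decide how much speed and accuracy each count

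*Protocol article*

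**What the plan says.** The section Virtual reality of the protocol article describes a five-ball touch-screen game and the parameters taken from it. It introduces the measure in question thus: "Among the parameters obtained from the game for the analysis of the learning process in children with DS, the error will be calculated". Two components are then described. The first is a length: "The error is obtained by calculating the distance between the center of the ball and the region touched". The second is a time: "the time interval between the moment that the ball changes color and the child's touch". The rule for combining them follows: "The total error is given by the sum of the time interval and the distance between points (touch and center of the ball"). The sum is taken touch by touch.

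The article gives no unit for either component, and no weight, standardisation or conversion factor.

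Two other places bear on how far the point reaches. Under Statistical analysis of results, the phase 3 rule for quantitative variables measured over time is that "comparisons of the EG and CG will be performed using repeated-measures ANOVA". Under Recruitment (Study 2), the trial is to be sized "considering brain activity as the primary outcome, a unidirectional alpha of 0.05 and a power of 80"%. Total error is not named in either place.

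**The concern.** A duration and a distance cannot be added until someone decides how many millimetres count as much as one second. A plain sum makes that decision silently, through the recording units. In milliseconds and millimetres the score is almost purely a speed measure; in seconds and millimetres it is almost purely an accuracy measure. Two analysts who both follow the text could therefore report different things under the same name.

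Any sum also lets a gain on one component offset a loss on the other. A child who becomes faster but less accurate may show no change.

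What is at stake is the interpretation of the learning analysis, and of any group comparison made on this score.

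**Working it through.** The article states no numerical value for total error, so there is no figure to reproduce. The check is dimensional, followed by an illustration.

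**Form of the score.** Write E = a·T + b·D, with T the response time and D the touch distance. The coefficients a and b depend only on the units. Changing both by the same factor merely rescales E. Changing their ratio (s to ms, or cm to mm) changes the relative weight of the components.

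**Inputs, all assumed.** SD of T: 0.4 s. SD of D: 5 mm or 6 mm. Components independent unless stated otherwise.

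**Share of variance due to time** = (a·sT)² / [(a·sT)² + (b·sD)²]

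| Units | SD of D = 5 mm | SD of D = 6 mm |
|---|---|---|
| ms + mm | 160000/160025 = 99.98% | 160000/160036 = 99.98% |
| s + cm | 0.16/0.41 = 39% | 0.16/0.52 = 31% |
| s + mm | 0.16/25.16 = 0.6% | 0.16/36.16 = 0.4% |

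**Ranking of two children.** Child A: 0.8 s and 2.0 cm. Child B: 1.4 s and 1.0 cm.
- s + cm: 2.8 against 2.4, so A is worse.
- ms + mm: 820 against 1410, so B is worse.

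The order reverses because A is faster and B more accurate.

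**Standardised difference between two groups**, d = (a·ΔT + b·ΔD) / √[(a·sT)² + (b·sD)²], here treating 0.4 s and 5 mm as SDs between children. Negative values mean less error in the first group.

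*First group 0.3 s faster, same accuracy:*
- ms + mm: −300/400.03 = −0.75
- s + cm: −0.3/0.640 = −0.47
- s + mm: −0.3/5.016 = −0.06

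The sign is the same throughout; only the size changes.

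*First group 0.3 s faster and 3 mm less accurate:*
- ms + mm: (−300 + 3)/400.03 = −0.74
- s + cm: (−0.3 + 0.3)/0.640 = 0.00
- s + mm: (−0.3 + 3)/5.016 = +0.54

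Here the sign changes too. If the components are correlated between −0.3 and 0.3, the s + mm value runs from +0.55 to +0.53 and the ms + mm value from −0.75 to −0.74, so the independence assumption matters little to this contrast.

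**SD-scaled sum.** Dividing each component by its own SD gives one answer whatever the units. In the last scenario d = (−0.75 + 0.60)/√2 = −0.11. Unit dependence has gone, but a speed gain of 0.75 SD and an accuracy loss of 0.60 SD now appear as almost nothing.

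**The case against.** The strongest reply is that little rests on this score. The article presents it as one of several game parameters. It does not appear in the hypotheses, among the assessments in Table 1, or in the primary and secondary results, and the sample size is to be based on brain activity. This stands, and it limits the severity.

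Second, a reader might infer that the comparison of active and sham tDCS depends on this score. The article does not say so. The repeated-measures ANOVA applies to quantitative variables at pre-intervention, post-intervention and one-month follow-up. Total error is defined for the five-ball training game, whereas Evaluation process describes a different task of touching indicated figures. Synchronising the game with EEG, EMG and motion capture makes use at evaluation possible, but it is not stated. The group comparison is therefore conditional.

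Third, a reader might infer that the same data could generally be made to show benefit, harm or no effect. That is too strong. If both components improve, or only one changes, every choice of units gives the same direction. Reversal needs speed and accuracy to move in opposite directions.

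Fourth, both components are described separately, correct and incorrect taps are also recorded, and nothing says that only the sum will be analysed. This too stands, and it is why the remedy is cheap.

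Finally, units may be fixed in a fuller document, so the article does not support a claim that they will be chosen after results are seen. Fixing units would make the score reproducible, but the weighting would remain an accident of those units. The combination rule is itself stated in the article, so the defect is in the text and is not an omitted detail.

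**Conclusion.** Wrong as written; minor severity. The stated rule adds two quantities of different dimension with no scaling, so the balance between speed and accuracy is arbitrary. That conclusion follows from the definition alone and needs no assumed figure.

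The size is illustrative only. It rests on assumed SDs and on independence when the variance is split. Spread between touches is also not the same as spread between children, so the variance shares show how the weighting moves and do not measure the effect on a trial comparison. Any comparison on the score would vary in size with the units. Its direction could vary only under a speed-accuracy trade-off. The listed results and the sample-size basis are untouched, and the documents do not support reading this as a threat to the trial's main conclusions.

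**What to change.** Replace the sum in the section Virtual reality by two separate parameters, response time and touch distance, each with its unit stated. Each is then unaffected by the units of the other, and a trade-off between them becomes visible.

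If a composite is still wanted, divide each component by its pooled baseline SD before adding, fix that rule before analysis, and always report both components beside it. The scaling removes the dependence on units but not the masking of a trade-off, so the composite should not stand alone.

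The cost is a change of wording. Both components are already obtained for every touch, so no new data are needed.

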## Results

### Primary result

1. Analyze the patterns of normality of upper limb movements (with 3D cinematics) in children with typical development and compare these patterns to those found in individuals with DS;

2. Correlate motion variables with kinematic 3D analysis, muscle activity with EMG and brain activity with EEG.

### Secondary results

1. After interpreting the movement, muscle, and brain patterns, investigate whether the parameters can be modified by a neuromodulation intervention protocol involving tDCS and VR motor training.

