## Objective/hypotheses

The objective of the study is to perform a comparative analysis of brain activity, muscle activity and upper limb kinematics during the execution of a manual motor task motivated by a VR game during anodal tDCS in children with DS. Psychomotor, muscle, and cognitive skills will be assessed before and after the intervention as well as at the 1-month follow-up. The objectives of the study will be to (I) correlate variables related to movement kinematics, motor activity, and brain activity, (II) compare the effects of transcranial stimulation in children with DS and those with typical development (TD), (III) determine the effects and possible adverse effects of anodal tDCS at an intensity of 1 mA administered during 20 min of training in children with DS, and (IV) determine the effects of different anodal tDCS montages in children with DS.

The null hypothesis of the study is that the results of ten sessions of anodal tDCS over the F3 region of the cortex during a motor task motivated by a VR game will not differ significantly from the results obtained from ten sessions of sham tDCS with the same training in children with DS. The alternative hypothesis is that the results of ten sessions of anodal tDCS over the F3 region of the cortex during a motor task motivated by a VR game will differ significantly from the results obtained from ten sessions of sham tDCS with the same training in children with DS.

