### Intervention protocol

The therapeutic intervention will only be performed in studies 2 and 3 of this protocol and will consist of a combination of tDCS and VR. The protocol will follow the safety procedures described in the literature for the use of tDCS in the population with neurological disorders [40–48]. Three 20-min sessions of tDCS concomitant with VR will be held for a total of ten sessions [42–48]. Training will be preceded by fitting and adapting the equipment to the participant. During the clinical trial, participants will be prohibited initiate therapeutic activities that may be similar in terms of the biomechanics used for the tests and intervention.

Since the protocol is an intervention with rehabilitation for motor and intellectual training, the participants will be asked to report participation in any other activities for the biomechanical investigation of the activity, as this population may need rehabilitation outside the study to maintain their daily routines. It will be up to the researchers to identify whether such activities may compromise the study results.

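### The randomised phase is to be sized on brain activity, but the outcome sections make non-randomised analyses primary and the tDCS effect secondary; two of the four listed objectives cannot be answered by the design

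*Protocol article*

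**What the plan says.** All references are to the protocol article.

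- **Hypothesis and design.** Objective/hypotheses sets active against sham tDCS in children with Down syndrome (DS), but speaks only of results and names no outcome. Study design describes phase 3 as a 1:1 randomised trial that expects superiority of the experimental group.
- **Sizing.** Recruitment, Study 2, will calculate the phase 3 sample size from the pilot group means, "considering brain activity as the primary outcome".
- **Primary result.** Item 1 is to "Analyze the patterns of normality of upper limb movements (with 3D cinematics) in children with typical development" and compare these with DS. Item 2 is to correlate kinematic, EMG and EEG measures.
- **Secondary results.** Once movement, muscle and brain patterns have been interpreted, the plan is to "investigate whether the parameters can be modified by a neuromodulation intervention protocol involving tDCS and VR motor training".
- **Analysis.** Statistical analysis of results compares the phase 3 groups on quantitative variables at three visits by repeated-measures ANOVA. It adds: "The level of significance will be set at 5% for all statistical tests".
- **Objectives.** Objective II is to "compare the effects of transcranial stimulation in children with DS and those with typical development (TD"; objective IV is to "determine the effects of different anodal tDCS montages in children with DS". Intervention protocol states: "The therapeutic intervention will only be performed in studies 2 and 3 of this protocol".

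**The concern.** A randomised trial needs one outcome, at one time, that carries its main claim and for which its sample size is calculated. Here the sizing text names one primary outcome and the outcome sections name others, and neither item under Primary result compares the randomised arms. A reader of the final report could not tell from this article whether a finding on EEG, EMG or kinematics, after treatment or at one month, was the result the trial was built to test. A favourable variable or visit could be brought forward after the data are seen. The sample size calculation would also be tied to an outcome that the outcome sections do not treat as primary.

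The objectives add a second contradiction. Two of the four ask questions for which the design collects no data.

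**Working it through.** The article gives no phase 3 sample size, effect size or standard deviation, because these await the pilot. There is therefore no stated figure to reproduce. The check is a comparison of sections and one short calculation.

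**1. Which outcome is primary?**

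| Section | Primary item | Compares active with sham? |
|---|---|---|
| Recruitment, Study 2 | Brain activity | Yes (experimental and control group means) |
| Primary result, item 1 | Upper limb kinematics, DS versus typical development (TD) | No, not randomised |
| Primary result, item 2 | Correlation of kinematics, EMG and EEG | No |
| Secondary results | tDCS effect on movement, muscle and brain parameters together (listed as secondary) | Yes |

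The first row cannot be squared with the other three as they stand. Brain activity appears under Primary result only as one side of a correlation, and the arm comparison appears only as secondary.

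**2. Is one phase 3 test singled out elsewhere?** The hypothesis names no outcome. The analysis section names no primary variable and no primary visit among pre-intervention, post-intervention and one month, and it gives every test the same 5% level. Nothing there resolves the conflict in step 1.

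**3. Size of the error rate.** Inputs: a 5% level per test (Statistical analysis of results) and three measurement domains, EEG, EMG and kinematics (Evaluation process). Assumptions: one test per domain, independent tests, and no effect of stimulation.

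Chance of at least one false positive = 1 − (1 − 0.05)^k. With k = 3: 1 − 0.95^3 = 1 − 0.8574 = 0.1426, or about 14%.

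Positive correlation lowers this figure. If the three tests were perfectly correlated it would fall to 5%. The range for three positively related tests is therefore 5% to about 14%.

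**4. Can objectives II and IV be answered?**

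- Objective II needs a stimulation effect in TD children. Stimulation takes place only in studies 2 and 3. Under Recruitment, study 2 enrols children who meet the DS criteria and study 3 follows from it; the Abstract confirms that the intervention part involves individuals with DS. TD children appear only in study 1, which has no intervention.
- Objective IV needs at least two montages. Randomization, Recruitment (Study 3) and the tDCS section describe one, with the anode over F3 and the cathode on the deltoid (the right deltoid in the last two). The sham group uses the same placement.

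**The case against.** The strongest defence is that the article covers a three-phase programme. Secondary results opens by referring to patterns that have already been interpreted, so the two outcome sections may list results in order: phase 1 first, the intervention afterwards. Brain activity would then be the phase 3 primary, as the sizing text says. This reading is plausible, but the article does not state it, and on this reading the outcome sections give phase 3 no primary of its own. It shows that the remedy is labelling and not redesign.

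A second defence is that EEG band, electrodes, time window and multiplicity procedure are commonly left to an analysis plan. That is fair, and their absence is not the point. The point is that published sections disagree on what is primary. An analysis plan that followed one of them would contradict another.

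Three stronger readings are tempting, and the documents do not support them:

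- *That the trial has no confirmatory comparison at all.* The hypothesis, the superiority aim, the nomination of brain activity and the planned ANOVA between groups all say otherwise.
- *That the power statement attaches to nothing.* Sample size names the Student's t-test formula, and Recruitment applies it to group means for brain activity. What remains open is the specific EEG variable and visit.
- *That the false positive rate is far above 14%.* The formula gives 40% for 10 tests and 64% for 20, but the article gives no such counts. Independence is also doubtful, since the signals are recorded together in one task and the plan itself intends to correlate them. Only three domains can be read from the text.

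**Conclusion.** The concern holds as an internal contradiction. An active-versus-sham superiority comparison is planned and brain activity is nominated for its sizing, but the outcome sections make two non-randomised analyses primary and the stimulation effect secondary. No single outcome and visit is consistently designated as the phase 3 primary. With one variable per domain, the chance of at least one false positive is up to about 14% instead of 5%. This rests on three tests and on independence, and it is lower if the measures are positively correlated.

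Objectives II and IV contradict the design outright, and that conclusion needs no assumption. It is a separate defect and does not bear on the error rate.

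**What to change.** 1. State outcomes by phase. Make the two items now under Primary result the phase 1 primaries.
2. For phase 3, name one EEG variable at one visit, active versus sham, as the primary. The sponsor should choose and justify both before pilot data are seen, so that the choice cannot follow the data. The article does not dictate the visit: its Discussion cites a study of tDCS with VR whose better alpha events were found especially at one month, so post-intervention should not be assumed.
3. Use that same variable and visit in both the sample size calculation and the analysis.
4. Label all other phase 3 variables and visits secondary or exploratory, or adjust for multiplicity. Any standard procedure will serve.
5. Delete objective IV. Delete objective II, or reword it to the DS-versus-TD comparison that phase 1 performs.

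The changes are to wording in the objectives, sizing, outcome and analysis sections, and they need no new visits or measurements. Phase 3 has no calculated sample size yet, so nothing has to be recalculated if this is done now. The price is that fewer results can be claimed as confirmatory at 5%.
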